### Bioanalytical methods

#### Drug concentration measurement

Blood is collected in 6 mL sodium-heparin blood tubes, centrifuged at 2000 g for 10 min within 1 hour from sampling. Aliquots of plasma is frozen in –70°C pending analysis, which will be made every 3 months^37 38^ at the Department of Clinical Pharmacology, Linköping University Hospital, Sweden (accredited ISO/IEC 17025:2018). Total drug concentration of isoniazid, acetyl isoniazid, rifampicin, pyrazinamide, and ethambutol will be determined by preparing samples with organic solvent protein precipitation in accordance with Fang *et al* and Han *et al*.^39 40^ The samples will be analysed with liquid chromatography on a reversed phase column ACQUITY UPLC BEH C18 Column, 130 Å, 1.7 µm, 2.1 mm X 50 mm a BEH C18 VanGuard pre-column and column in-line Filter (Waters Corporation, Milford, USA) and with tandem-mass spectrometry MS detection using a tandem quadrupole mass spectrometer (Xevo TQ MS, Waters) in positive electrospray ionisation mode with the following quantification traces; isoniazid 137.96>121.04, acetyl isoniazid 180.0>121.0, rifampicin 823.30>791.416, pyrazinamide 123.95>54.1, and ethambutol 205.1>116.15. The analytic range for isoniazid is 0.25–8 mg/L, acetyl isoniazid 0.25–8 mg/L, rifampicin 2.5–80 mg/L, pyrazinamide 2.5–80 mg/L, and ethambutol 0.25–8 mg/L. The drug concentration analysis method is validated according to EMA guideline on bioanalytical method validation.^41^ For the quality controls at 0.75 mg/L and 6 mg/L for isoniazid, acetyl isoniazid and ethambutol the inter-day accuracy is between 95.8% and 99.9% and with a precision between 7.7% and 10.5% and for pyrazinamide and rifampicin quality controls at 7.5 and 60 mg/L the accuracy is between 92.3% and 97.6% and precision between 9.3% and 11.8%. Intra-day at 0.75 mg/L and 6 mg/L for isoniazid, acetyl isoniazid and ethambutol gave accuracy between 86.7% and 95.6% and a precision of 0.6%–5.2% and for pyrazinamide and rifampicin at 7.5 and 60 mg/L an accuracy between 92.3% and 108.8% and precision of 2.2%–7.5%.

### Microbiology

#### Time to culture positivity

Sputum samples are treated according to routine and are carried out at a biosafety level 3 laboratory at the accredited TB laboratory of the Department of Clinical Microbiology at Linköping University Hospital, Sweden. In short, following treatment of sputum with sputolysine, samples are centrifuged and resuspended in 1.5% NaOH-SDS with 2 mm glass beads and vigorously stirred using a vortex mixer. After neutralisation by 0.09% sulfuric acid samples are washed in phosphate buffer and added to MGIT-tubes according to the instructions by the manufacturer. The MGIT-tubes are incubated using BACTEC MGIT 960 (Becton Dickinson, Lakes, NJ, USA) at 37°C for up to 42 days. When growth is detected TTP is automatically recorded, *Mtb* isolates are stored at −70°C awaiting minimal inhibitory concentration (MIC) determination.

#### Minimum inhibitory concentrations

Previously stored *Mtb* isolates (−70°C) from study participant obtained before treatment initiation will be used for MIC determination of first-line drugs. MIC determination will be performed for rifampicin, isoniazid and ethambutol by broth microdilution in accordance with the EUCAST reference method for *Mtb*, and when applicable additional group A drugs as displayed in figure 2.^42^ MIC is defined as the lowest antibiotic concentration without growth when the 1:100 diluted controls show visual growth. *Mtb* H37Rv ATCC 27294 will be included as an internal quality control in each batch. Breakpoints established by the Clinical and Laboratory Standards Institute are used for drug susceptibility testing (DST) of isolates for rifampicin, isoniazid, and ethambutol in broth microdilution plates (1, 0.12 and 8 mg/L, respectively).^43^ Routine DST of first-line drugs and MIC determination of pyrazinamide are performed in MGIT as previously described with WHO-based critical concentrations of antibiotics for routine DST (rifampicin 0.5, isoniazid 0.1, pyrazinamide 100, and ethambutol 5 mg/L) and by using serial twofold dilutions of antibiotics for pyrazinamide MIC testing.^44^ Pyrazinamide will also be included in the reference method (pH 5.9) as an internal validation (figure 2).

**Figure 2 F2:**
[figure not shown]
Plate outline for MIC determination by broth microdilution using the EUCAST reference method. dH_2_O, distilled water; EMB, ethambutol; EUCAST, European Committee on Antimicrobial Susceptibility Testing; GC, growth control; INH, isoniazid; LEV, levofloxacin; LIN, linezolid; MIC, minimal inhibitory concentrations; PZA, pyrazinamide; RIF, rifampicin.

### Data analysis plan

Study monitoring is performed regularly by the regional support unit for clinical trials, Forum Östergötland, at all study sites before study opening, during recruitment period and at study closure. Obtained study data are entered in electronic case record forms and managed by using REDCap (research electronic data capture) 45 46 hosted at Linköping University and at time of data analysis transferred to a database for statistical processing.

The primary outcome is AUC_0-24h_ of pyrazinamide in the intervention arm and the main secondary outcome is the incidence and severity of AEs. The distribution of AUC_0-24h_, C_max_ and PK-PD indices (AUC_0-24h_/MIC, C_max_/MIC) will be visualised separately for the two study arms. Difference in drug exposure will be explored by Mann-Whitney’s U test. A p≤0.05 will be considered statistically significant. The PK-PD indices based on drug exposure at day 14 for the investigational products (pyrazinamide and rifampicin) will be correlated to tentative PK-PD targets derived from the literature on human studies such as the suggested AUC_0-24h_ >363 mg*hour/L and AUC/MIC >8.42 for pyrazinamide.^47^ Associations between drug exposure and liver laboratory assessments will be analysed by using Spearman rank correlation. The incidence of minimum grade two AE and SAE will be presented in frequency tables and correlation graphs on exposure-tolerability. Nonlinear mixed effects modelling will be utilised to derive a population PK model for high-dose pyrazinamide. A model-informed precision dosing approach will be derived in order to be able to predict optimised dose given information from early PK sampling. An earlier developed model-informed precision dosing approach for high-dose rifampicin^48 49^ will be applied to evaluate the accuracy in the high-dose predictions. The sample size of 10 participants in the control group and 30 in the intervention group will enable sufficient descriptive PK data of the combined high-dose pyrazinamide and rifampicin regimen accounting for the expected larger PK-variability in this group compared with the control group.^49^ Applying EBA as one of the safety endpoints, we estimate 30% difference in EBA between the study arms (80% power, p=0.05), based on previous unpublished data of TTP-dynamics observed in our observational cohort study^24^ combined with EBA data from the literature.^10 11 50^ Randomisation is performed in blocks stratified by gender and will continue until 10 individuals in the control arm and 30 individuals in the experimental arm have completed PK sampling day 14. The randomisation scheme was done with the statistical programme R V.4 (the R foundation) by an independent statistician, uploaded into the CRF-programme REDCap^45 46^ and blinded to the person who includes patients. Resistance to first-line drugs is rare in Sweden and multidrug resistant (MDR) TB accounted for 1.8% of all new TB cases 2019^29^ and the majority of the drug resistant cases are detected early. Thus, late exclusions from the study based on detected drug resistance, are expected to be negligible. A modified intention-to-treat analysis will be performed for patients who may miss follow-up in addition to a per-protocol analysis.

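### The exposure comparison uses an unstratified Mann-Whitney test although randomisation was stratified by gender, and PK-PD indices cannot be correlated with fixed target values

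*Protocol article*

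**What the plan says.** All of the relevant text stands in the Data analysis plan section of the protocol article.

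- Primary outcome: "The primary outcome is AUC_0-24h_ of pyrazinamide in the intervention arm". This is a single-arm quantity.
- Between-arm comparison: "Difference in drug exposure will be explored by Mann-Whitney"'s U test, followed by "A p≤0.05 will be considered statistically significant". No strata or covariates are named.
- Allocation: "Randomisation is performed in blocks stratified by gender".
- Targets: the day-14 indices for pyrazinamide and rifampicin "will be correlated to tentative PK-PD targets derived from the literature on human studies". The examples given are "AUC_0-24h_ >363 mg*hour/L and AUC/MIC >8.42 for pyrazinamide".
- Size: "The sample size of 10 participants in the control group and 30 in the intervention group" is justified as giving sufficient descriptive PK data, "accounting for the expected larger PK-variability in this group compared with the control group".

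The section also plans plots of the exposure distributions by arm and a population PK model for high-dose pyrazinamide. Individual AUC and Cmax come from non-compartmental analysis (Study outline section).

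**The concern.** There are two separate faults in what the section states.

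**Stratification.** Balancing the arms on gender removes gender from the true variability of the between-arm contrast. An unstratified rank test does not know this. It judges the contrast against a spread that still contains the gender difference. If exposure differs by gender, the test rejects too rarely and wastes part of a small sample with only 10 controls.

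**Targets.** A target such as 363 is the same number for every patient. A correlation needs variation on both sides, so the stated analysis has no answer. What a reader will want is how many patients reach the target, and the article does not name that measure.

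**Working it through.** **Inputs from the protocol article.** There are 10 control and 30 intervention patients, stratified by gender, with a threshold of p≤0.05 (two-sided assumed). Table 2 gives pyrazinamide 40 against 20–30 mg/kg, so dose ratios run from 40/30 = 1.33 to 40/20 = 2.0, with 40/25 = 1.6 at mid-range. Isoniazid and ethambutol doses are the same in both arms.

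**Assumptions, because the article gives no figure.** Log-normal exposure with CV 0.3 or 0.5; a gender effect of 1.0-, 1.25- or 1.5-fold; 40% women; blocks of 4.

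**The plan's own figure.** The only power statement (80% for a 30% difference) concerns early bactericidal activity, not exposure, and comes without an SD. Solving backwards, (1.960 + 0.842) × √(1/10 + 1/30) = 1.02 SD, so it needs a CV of about 0.30/1.02 = 0.29. It does not bear on this point.

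**Step 1: hand check of the conservatism (CV 0.3).** Within-gender log variance is ln(1 + 0.3²) = 0.0862. The between-gender part is 0.4 × 0.6 × (ln effect)².

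- 1.25-fold: 0.24 × 0.2231² = 0.0120. SD ratio √(0.0862/0.0982) = 0.937. Effective critical value 1.960/0.937 = 2.09, so type I error is about 3.7%.
- 1.5-fold: 0.24 × 0.4055² = 0.0395. SD ratio √(0.0862/0.1257) = 0.828. Effective critical value 2.37, so type I error is about 1.8%.

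**Step 2: simulation.** There were 4,000 runs under the null and 2,000 otherwise. Entries are rejection rates.

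| True ratio | CV | Gender effect | Mann-Whitney | van Elteren |
|---|---|---|---|---|
| 1.0 | 0.3 | 1.0 | 4.6% | 5.2% |
| 1.0 | 0.3 | 1.25 | 3.7% | 5.3% |
| 1.0 | 0.3 | 1.5 | 1.7% | 4.5% |
| 1.3 | 0.3 | 1.0 | 63.4% | 63.2% |
| 1.3 | 0.3 | 1.25 | 58.9% | 63.0% |
| 1.3 | 0.3 | 1.5 | 43.0% | 62.3% |
| 1.6 | 0.3 | 1.25 | 97.6% | 98.4% |
| 1.6 | 0.3 | 1.5 | 95.4% | 98.9% |
| 1.6 | 0.5 | 1.0 | 71.5% | 70.2% |
| 1.6 | 0.5 | 1.5 | 63.6% | 71.2% |

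Monte Carlo error is up to √(0.25/2000) = 1.1 points. Repeat runs agree:

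- At ratio 1.3 and CV 0.3, Mann-Whitney power is 56–57% (1.25-fold) and 43–45% (1.5-fold), against about 62% for van Elteren.
- At ratio 1.6, CV 0.5 and a 1.5-fold effect, the loss is about 6 points.

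With no gender effect the two tests are equal within simulation error, so stratifying costs nothing visible.

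**Step 3: precision of an estimate.** The 95% half-width factor for a geometric mean ratio is exp(t × s × √(1/10 + 1/30)), with s = √ln(1 + CV²) and t = 2.024.

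- CV 0.3: exp(2.024 × 0.2936 × 0.3651) = 1.24.
- CV 0.5: exp(2.024 × 0.4724 × 0.3651) = 1.42.

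In the simulation the gender-adjusted factors were 1.24 and about 1.41–1.42. Without adjustment at a 1.5-fold gender effect they were 1.30 and 1.46.

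**Step 4: unequal variability.** The plan expects more variability in the larger arm. Suppose CV 0.3 in control and 0.5 in intervention (log variances 0.0862 and 0.2231).

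- True SE: √(0.0862/10 + 0.2231/30) = 0.127.
- Pooled variance: (9 × 0.0862 + 29 × 0.2231)/38 = 0.1907, giving SE √(0.1907 × 0.1333) = 0.159.

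A common-variance model would then give an interval about 26% too wide on the log scale.

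**Step 5: targets.** A Spearman coefficient between 30 values and the constant 363 returns no value. A proportion is computable. Illustrative exact 95% intervals are 27/30 = 90% (73–98%), 24/30 = 80% (61–92%) and, in the control arm, 5/10 = 50% (19–81%).

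**The case against.** The strongest reply is that this is an exploratory comparison in a condensed article. Estimates, intervals and adjustment often sit in a fuller protocol or SAP that is not shown. That is right as far as omissions go: their absence here is not a fault. It does not cover the two things the article does state, namely a test without strata and a correlation with constants.

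Correlated is probably loose wording for compared, since the targets are written as thresholds and the next sentence names Spearman's method where a coefficient is meant. I accept that. It remains the wrong word for the only stated link between indices and targets.

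Three stronger readings are tempting, and the document does not support them.

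- *The trial cannot answer its primary PK question.* The primary outcome is intervention-arm AUC, which rests on non-compartmental analysis, the plotted distributions and the population PK model. Neither fault touches it.
- *Equal exposure is a pointless null and significance is assured.* Isoniazid and ethambutol are measured too and have equal doses in both arms, so for them the null is meaningful. For pyrazinamide, Mann-Whitney power at ratio 1.6 is 95–98% at CV 0.3 but only 64–72% at CV 0.5.
- *Ignoring the strata makes the test invalid.* It errs on the conservative side. Type I error is not inflated.

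**Conclusion.** The point holds as a modest improvement to a stated method plus a correction of wording. The unstratified test loses efficiency only if exposure differs by gender, and the article gives no gender effect.

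Under the assumed CV of 0.3, gender effects of 1.25- and 1.5-fold bring type I error to about 4% and 1 to 2%. At a true ratio of 1.3 they cost about 5 and 17 to 19 points of power. That ratio is relevant to pyrazinamide if control doses lie near the top of their range, and to modest differences in the companion drugs. For a 1.6-fold pyrazinamide ratio the loss is under 1 point at CV 0.3 with a 1.25-fold effect, and 6 to 8 points at CV 0.5 with a 1.5-fold effect.

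The correlation with fixed thresholds cannot be computed under any assumption.

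**What to change.** 1. Replace the Mann-Whitney test with a gender-stratified rank test (van Elteren). Alternatively, fit a log-scale linear model with arm and gender and report the geometric mean ratio with its 95% interval. If the model is used, allow the variance to differ by arm.
2. Replace the sentence on correlation with targets by the number and proportion of patients attaining each target at day 14, by arm, with exact 95% intervals.

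Neither change needs new data, visits or patients. The cost is wording, and in the model one degree of freedom (residual 38 to 37).

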### Study participants

A total number of 40 evaluable patients will be included. Study inclusion and exclusion criteria are listed in table 1.

**Table 1 T1:** Inclusion and exclusion criteria in HighShort-RP

Inclusion criteria	Exclusion criteria
Adult (≥18 years)	Treated for TB within the last year.
Pulmonary TB confirmed by PCR and/or culture for *Mtb*	Molecular or phenotypic resistance to any of the first-line oral drugs
Eligible for first-line TB treatment, but not yet started treatment	Miliary TB or advanced pulmonary TB with sputum smear grade three or advanced TB on chest X-ray according to National Tuberculosis Association (1961)^30^ defined by one or more of the following radiological findings: Cavitation of >4 cm diameter. Disseminated lesions of slight to moderate density which extend throughout the total volume of more than one lung (uni- or bilateral). Radiological signs of dense and/or confluent lesions affecting >1/3 of one lung or in both lungs combined
Hiv-negative	Any other infectious disease of such significance that urgent treatment is required
BMI >17	Ongoing treatment with other medication where treatment with rifampicin can interact with the medication and compensatory drug adjustments cannot be made
Written informed consent to participate in the study	Previously known allergy to any of the first-line drugs or other contraindications according to the Summary of Product Characteristics of rifampicin, isoniazid, pyrazinamide and ethambutol
Fertile women must agree to use a barrier contraceptive during the study and have a negative pregnancy test on inclusion	Immunocompromised defined as primary or secondary immunodeficiency including immunosuppressive treatment such as chemotherapy, immunomodulating agents, corticosteroids equivalent to ≥15 mg prednisolone
	Known liver disease or aspartate aminotransferase or alanine aminotransferase >1.5 times the upper normal level
	Heart failure (NYHA class III and IV)
	Kidney failure (eGFR <50 mL/min)
	Dysregulated diabetes mellitus
	Alcohol or drug abuse
	Pregnancy or breast feeding
	Bodyweight <35 or >90 kg

BMI, body mass index; eGFR, estimated glomerular filtration rate; *Mtb*, *Mycobacterium tuberculosis*; NYHA, New York Heart Association; TB, tuberculosis.

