**Figure 1 F1:**
[figure not shown]
The study outline in the flow chart arrow reflects study activity identical for the intervention and control group. After 4 months treatment, the intervention group is followed up according to the follow-up information found in the bottom of the flow chart arrow, meanwhile the control group is followed up according to routine care (not included in the picture). Study participants are provided with a drug diary to record concomitant drugs, food intake and potential side effects during the treatment. Sputum samples are collected regularly during the study to assess time to positivity in BACTEC MGIT 960 for mycobacterial liquid culture. Rich blood sampling for measurement of drug concentrations is collected on the day of the first dose and after 14 days of treatment. Changes in clinical status is assessed by a clinical scoring tool (TBscore II) in addition to evaluation by chest X-ray and/or thoracic CT. Safety data are monitored closely during the first four study months and is based on urgently reported serious adverse events (AEs), AE questionnaire, medical records, regularly surveillance of blood chemistry and during the first 2 weeks analysis of ECG. The final treatment outcome, according to WHO definitions and occurrence of relapse, is registered for both study arms after treatment completion. TB, tuberculosis.

After providing informed consent patients are screened for eligibility to participate in the study based on the inclusion and exclusion criteria (table 1). A review and registration of the patient’s clinical status and symptoms is made, and any pre-existing symptoms and findings are recorded for future reference as potential adverse event (AE) from high-dose pyrazinamide and rifampicin can overlap with the symptoms of active TB. Provided all the inclusion criteria and none of the exclusion criteria are fulfilled according to the responsible physician, the study participant is electronically randomised in a 1:3 ratio to either open-label standard first-line TB treatment for 6 months or to a shortened treatment of 4 months in the intervention group. The higher doses utilised in the intervention group are 40 mg/kg of pyrazinamide (for 8 weeks) and 35 mg/kg of rifampicin (for 4 months) and with standard dosing of isoniazid (5 mg/kg for 4 months) and ethambutol (15–20 mg/kg for 8 weeks) (table 2). Dose adjustment based on changes in body weight will be evaluated after 2 weeks of therapy.

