## Ethics and dissemination

This study has been approved by the Swedish Ethical Review Authority (approval number 2020-00761) and the Swedish Medical Products Agency (approval number 5.1-2019-105207 and EudraCT number 2019-003721-25). Prior to the study opening, a designated study team of nurses, physiotherapists (training of study nurses in collection of induced sputum), laboratory staff and clinical doctors participated in training sessions of the study protocol which included study-specific procedures and ethical considerations. Study initiation meeting and the main training sessions were led by the coordinating principal investigator assisted by the support unit for clinical trials Forum Östergötland. Physicians and nurses in the study team have documented training in Good Clinical Practice (GCP) and the study is performed in accordance with GCP and the Declaration of Helsinki. Informed consent is obtained from each study participant by a physician prior to any study-specific activity. Inclusion of patients in the study is restricted to the available set of written informed consent translated into selected languages. In addition and when required, an interpreter will be used for providing study information and to translate during study visits. Study participants are free to withdraw from the study at any time and will at that point be offered treatment according to standard of care. The safety of combined high-dose pyrazinamide (40 mg/kg) and rifampicin (35 mg/kg) has not been studied in humans before. However, TB treatment with rifampicin 35 mg/kg given to 63 patients for 12 weeks has been proven safe.^11^ Furthermore, data were recently presented on exposure-tolerability of 2 weeks treatment with rifampicin 40 mg/kg (n=15) and 50 mg/kg (n=17) where the dose of 40 mg/kg was safe and tolerable.^26^ In early studies on lengthy treatments of pyrazinamide beyond 8 weeks, increased liver markers, jaundice and arthralgia were associated with higher doses of pyrazinamide.^51^ In a meta-analysis comparing rates of AEs between different doses of pyrazinamide, the frequencies of hepatotoxicity were 0.042 (95% CI 0.026 to 0.067) for 30 mg/kg, 0.055 (95% CI 0.031 to 0.094) for 40 mg/kg and 0.098 (95% CI 0.047 to 0.193) for 60 mg/kg, suggesting a considerable proportion of hepatoxicity rates may be idiosyncratic rather than dose-dependent.^52^ According to a meta-analysis (n=4490), liver toxicity did not seem to be dose-dependent until pyrazinamide exposures exceeded a weekly AUC of 5000 mg*hour/L^53^ compared with an AUC of 363 mg*hour/L on standard dosing.^47^ Recently, a patient-level data analysis where patients received rifampicin (range 10–35 mg/kg), pyrazinamide (range 20–30 mg/kg), plus two companion drugs, found liver toxicity to be rare (3.9% with grade 3 or higher liver function tests, LFT), and no relationship was observed between pyrazinamide C_max_ and LFT levels.^25^ Furthermore, currently used doses of 30–40 mg/kg pyrazinamide daily as part of MDR-TB treatment are well tolerated.^54^ In summary, we consider it safe for patients to participate in our clinical trial and study participants will be closely monitored regarding potential side effects including weekly measurement of LFT during the first 8 weeks when high-dose pyrazinamide and rifampicin are combined. As this is a phase II clinical trial exploring increased dosing of already approved and widely used drugs, the review authorities did not require a data safety and monitoring board.

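### The exposure–liver analysis is a two-variable Spearman correlation with no named adjustment for the pre-treatment AST and ALT that eligibility requires; a partial rank correlation would be the better method

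*Protocol article*

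**What the plan says.** The Data analysis plan of the protocol article gives one sentence on this analysis: "Associations between drug exposure and liver laboratory assessments will be analysed by using Spearman rank correlation". It names no covariate, partial correlation or baseline term. It does not say which liver variable is meant (single visit, peak, change or multiple of the upper normal level) or whether one arm or both are used. The significance level in the same section is general: "A p≤0.05 will be considered statistically significant".

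Pre-treatment AST and ALT exist by design. Table 1 excludes "Known liver disease or aspartate aminotransferase or alanine aminotransferase >1.5 times the upper normal level", and the Study outline has eligibility checked before randomisation: "After providing informed consent patients are screened for eligibility to participate in the study based on the inclusion and exclusion criteria". The Study outline also has pre-existing findings recorded as a reference for judging later adverse events, but the article does not link that record to the correlation. Under Ethics and dissemination, the on-treatment monitoring is "weekly measurement of LFT during the first 8 weeks when high-dose pyrazinamide and rifampicin are combined".

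The trial plans 10 control and 30 intervention patients. The main secondary outcome is the incidence and severity of adverse events. The exposure–liver correlation sits beside it as a supporting exploration.

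**The concern.** A patient's on-treatment transaminase level may partly reflect the level held before the first dose. A two-variable rank correlation treats that part as noise. If baseline liver status also happens to be related to drug exposure, the same part is counted as a drug association. A two-variable coefficient cannot separate the two, whereas conditioning on the measured baseline can.

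This is the only exposure–liver analysis with a named statistical method, in a trial whose article says the combined high doses have not been studied in humans before. With about 30 patients there is little power to spare, so leaving out a measured covariate could weaken the analysis just where it is meant to inform.

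**Working it through.** **Inputs from the article.** 30 intervention patients; 40 in total if both arms are pooled, which the article does not state. Significance at 0.05, taken as two-sided because sidedness is not given.

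**Inputs assumed, because the article gives none.** ρ, the correlation of baseline with on-treatment value: 0 to 0.7. True standardised exposure effect: 0.4. For the false-positive check, c, the correlation of exposure with baseline liver value: 0.3.

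**No plan figure to reproduce.** The article states no power or detectable size for this correlation. By the Fisher approximation, 80% power needs a rank correlation of tanh[(1.960 + 0.842) × √(1.06/(n − 3))]:
- n = 30: tanh(2.802 × √(1.06/27)) = tanh(0.555) = 0.50
- n = 40: tanh(2.802 × √(1.06/37)) = tanh(0.474) = 0.44

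**Step 1: power.** Model: on-treatment value = ρ × baseline + 0.4 × exposure + noise, total variance 1, exposure independent of baseline. The plain correlation is 0.4 whatever ρ is. The correlation given baseline is 0.4/√(1 − ρ²):
- ρ = 0.3: 0.4/√0.91 = 0.419
- ρ = 0.5: 0.4/√0.75 = 0.462
- ρ = 0.7: 0.4/√0.51 = 0.560

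Simulated power at n = 30:

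| ρ | Plain Spearman, raw value | Spearman, change score | Partial Spearman given baseline |
|---|---|---|---|
| 0.3 | 55% | 41% | 57% |
| 0.5 | 55% | 55% | 66% |
| 0.7 | 55% | 80% | 83% |

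The gains from adjustment are 57 − 55 = 2, 66 − 55 = 11 and 83 − 55 = 28 points. At ρ = 0, plain is 55% and partial 53%, so adjustment loses about 2 points. If both arms were pooled (n = 40), plain power is 69% against 72%, 80% and 93% adjusted.

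A second parametrisation holds the baseline-adjusted correlation at 0.5 instead. At n = 30, plain against adjusted power is then 79% v 77% (ρ = 0), 72% v 75% (0.3), 61% v 74% (0.5) and 46% v 73% (0.7). The pattern is the same.

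**Step 2: false positives.** No true drug effect, c = 0.3. The plain correlation is then c × ρ = 0.09, 0.15 and 0.21 for ρ = 0.3, 0.5 and 0.7. For a change score it is −c × √((1 − ρ)/2) = −0.18, −0.15 and −0.12. Given baseline it is zero. Simulated rejection rates at n = 30:

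| ρ | Plain, raw value | Change score | Partial |
|---|---|---|---|
| 0.3 | 7% | 14% | 5% |
| 0.5 | 11% | 12% | 5% |
| 0.7 | 18% | 9% | 5% |

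The change score errs in the opposite direction to the raw value, so it does not repair the problem. At ρ = 0.3 it also loses 14 points of power (41% v 55%).

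**The case against.** The strongest reply is that the article is silent rather than wrong. It does not define the liver variable, and the full protocol or analysis plan may do so, perhaps as a change from baseline. This stands in part: a reader might infer that the trial ignores baseline liver status, and the text does not support that. The missing definition is not itself a fault in a condensed article. What remains is that a method is named, it takes two variables, and neither natural choice of variable (raw value or change score) does what conditioning on baseline does.

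Second, both harms rest on correlations that the article does not give. This also stands. Excluding known liver disease and transaminases above 1.5 times the upper normal level narrows the baseline spread, which would tend to lower ρ and the gain. Idiosyncratic flares, which the article itself raises, would be poorly predicted by near-normal baselines, and the simulation models neither truncation nor flares. A reader might infer that the exposure relation will be diluted, or that a baseline difference will pass for toxicity. Neither can be asserted as fact.

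Third, the analysis is exploratory. Adverse events are graded and tabulated separately, no dose or continuation decision is tied to this correlation, and the article acknowledges the small sample. The safety argument cites several outside sources, so it should not be said to hang on this result. This limits the importance of the point but does not make the plain correlation the better choice.

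**Conclusion.** The point holds in a conditional form. The named two-variable Spearman correlation makes no stated use of pre-treatment AST and ALT that every patient must have. Whether this costs anything depends on how closely on-treatment values follow baseline: negligible at a correlation of 0.3, material at 0.5 and above, and slightly in favour of the plain test at zero. The inflated false-positive rate arises only if exposure is itself correlated with baseline liver values, for which the article gives no figure. All sizes assume roughly normal variables, a raw on-treatment value and 30 patients.

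A reader might conclude that the safety assessment is invalid or that its result will be misleading. The article does not support that: this is supporting exploration, and baseline findings are recorded for adverse-event assessment. It is an inexpensive improvement worth making before the data are analysed.

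**What to change.** Replace the sentence on liver tests in the Data analysis plan with wording such as: *As an exploratory analysis, the association of drug exposure with on-treatment AST and ALT will be estimated by partial Spearman rank correlation given the pre-treatment value of the same test, with a 95% confidence interval.* A regression of ranks with the baseline rank as covariate serves equally well. State in the analysis plan which on-treatment summary is used and whether the arms are pooled. Include bilirubin only if a pre-treatment value is collected; the eligibility criterion names only AST and ALT. Do not substitute a plain change from baseline.

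Cost: one sentence and one degree of freedom, no new AST or ALT data, and at most about 2 points of power if baseline proves uninformative.
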